### Statistical analysis

The unit of analysis and inference will be an adolescent. Comparison of the characteristics of teens and their parents between intervention and control groups will be made using the chi-square test for categorical variables and Student t-test for continuous variables to describe the study population and ascertain similarity of both groups at baseline measure.

Scores for each outcome variable will be calculated according to the scoring algorithms. Differences in baseline and post-intervention stages for outcome variables will be compared within each group. Differences between groups will be compared using the differences-in-differences (D-in-D) estimator [34]. The generalized linear model (GLM) will be used to assess changes in each outcome variable controlling for baseline measures and study covariates. GLM methods allow for modeling the correlation of the repeated observations on the same subjects [35].

The analysis will be performed according to the intention-to-treat approach. Missing measurements due to a participant’s withdrawal from the study will be replaced with the most recent observations; p value <0.05 will be considered as statistically significant. The analysis will be performed using Stata v.11.0 statistical software (Stata 11.0, Stata Corp; College Station, TX).

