## Methods

A field trial of one intervention and one comparison group with ex-ante and ex-post measurements will be conducted in two public secondary schools in the Iztapalapa Delegation in Mexico City. A delegation represents a geo-political area; Mexico City is divided into 16 delegations. Compared to the rest of the delegations, Iztapalapa has less favorable socioeconomic indicators [24]. The intervention will take place in one school and the second school will serve as a comparison group where we will observe the usual sex education being offered. The schools will be selected through simple random sampling from the list of public secondary schools in Iztapalapa. The study population will consist of adolescents between 14 and 15 years of age who are in the third year of secondary school and agree to participate through informed consent. Parents are also required to sign written informed consent.

The project was authorized by the National Research and Ethics Committee of the Mexican Institute of Social Security (R-2014-785-033), the Research and Ethics Committee of the Hospital Infantil de Mexico Federico Gómez (HIM 2015-066) and the General Directorate of Technical Secondary Education of the Secretary of Education.

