### Sample size

Sample size was calculated using the software “A-priori Sample Size Calculator for Multiple Regression” (available at: http://www.danielsoper.com/statcalc3/calc.aspx?id=1). Effect of the intervention will be accessed by multiple regression analysis considering possible confounders due to the quasi-experimental nature of the study design. We considered the medium size effect for F-test (f2) of 0.15, alpha of 0.05, beta of 0.90, and 15 covariates. The number of teens by group, assuming a drop-out rate of 25 %, will be 200.

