Also, several limitations can be noted. (i) The proposed study design is ‘quasi-experimental’ with one intervention and one comparison group, with ex-ante and ex-post measurements. Therefore, the assignment of teens to the intervention and control groups will not be random. This could lead to interpretation problems if baseline measurements differ between groups. Furthermore, in order to address baseline differences between intervention and control group we proposed to perform the D-in-D estimator in the framework of a generalized linear regression model. (2) Due to financial feasibility issues we could not use an extensive (6 months or longer) follow-up and evaluate health-related outcomes such as pregnancies and sexually transmitted infections.

In conclusion, it is justifiable to design and evaluate an Internet-based educational strategy to prevent risky sexual behaviors in Mexican adolescents in order to provide a new, large scale, easily implemented and preventive tool.

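### With one school per arm and the adolescent as the unit of inference, school and intervention cannot be separated, and the between-group p values omit between-school variance

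*Protocol article*

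**What the plan says.** The opening of Methods fixes the allocation: "The intervention will take place in one school and the second school will serve as a comparison group". The same section says how the two schools are found: "The schools will be selected through simple random sampling from the list of public secondary schools in Iztapalapa". That concerns which schools enter the study. The section does not say how the two are then divided between the arms.

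Statistical analysis sets the level of inference: "The unit of analysis and inference will be an adolescent". For the contrast between arms it says: "Differences between groups will be compared using the differences-in-differences (D-in-D) estimator". A generalized linear model then adjusts for baseline and covariates. The only correlation mentioned is within a person: "GLM methods allow for modeling the correlation of the repeated observations on the same subjects". No school or classroom term is stated. The analysis is by intention to treat, withdrawals are filled with the last available value, and significance is judged at 0.05.

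Sample size is an individual-level regression calculation with "medium size effect for F-test (f2) of 0.15, alpha of 0.05, beta of 0.90, and 15 covariates". It gives 200 teens per group after allowing for 25% drop-out, and contains no ICC or design effect.

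The limitations in the Discussion admit that "the assignment of teens to the intervention and control groups will not be random" and give this answer: "in order to address baseline differences between intervention and control group we proposed to perform the D-in-D estimator".

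**The concern.** The intervention is assigned to a whole school, but the test treats about 400 adolescents as independent. Pupils of one school share teachers, timetable, peers and local events, so their scores may move together for reasons unrelated to the web page.

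The article itself gives reasons to expect such movement. The comparison school continues its usual sex education, and the Background says that the quality and delivery of such teaching are not known. Retention works partly through shared channels, namely classroom reminders and teacher involvement.

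Two things are at stake:

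- **Attribution.** Anything that changes in one school but not the other between baseline and month 4 is added to the estimated effect and cannot be told apart from it.
- **Error rate.** The standard error of the between-arm contrast has no between-school component, so the 0.05 rule need not hold its 5% level.

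**Working it through.** **Inputs from the article**
- Schools: 2, one per arm (Methods).
- Teens per school: 200 recruited, or 200 × 0.75 = 150 if 25% drop out (Sample size). Because missing values are carried forward under intention to treat (Statistical analysis), the number analysed should be nearer 200, so both are shown.
- Threshold: two-sided 0.05.

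**Assumed input**
- ICC of the analysed change score, given baseline and covariates. The article gives none; the range used is 0.001 to 0.05.

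**The plan's own figure.** Reading the stated beta of 0.90 as power, a regression F-test with f2 = 0.15, alpha 0.05 and 15 predictors needs 171 teens in total. Dividing by 0.75 gives 228 (114 per group); multiplying by 1.25 gives 214 (107 per group). The stated 200 per group is not reproduced. This does not drive the present point: 400 exceeds 228, so individuals are not short. What matters here is that the formula assumes independent individuals.

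**Step 1: degrees of freedom at school level.** 2 schools − 2 arms = 0. Between-school variance cannot be estimated. More pupils, a random school effect or cluster-robust errors cannot supply it. This step needs no assumption.

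**Step 2: what difference-in-differences removes.** Write the mean change in a school as intervention effect + school-specific change + sampling error. A constant school level cancels when baseline is subtracted. The school-specific change does not cancel, and with one school per arm it is added in full to the estimated effect.

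**Step 3: size, if the school-specific change varies at random between schools.** Design effect DE = 1 + (m − 1) × ICC. The standard error (SE) should be multiplied by √DE. Actual two-sided error = 2 × [1 − Φ(1.96/√DE)].

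| ICC (assumed) | DE, m=150 | √DE | Actual error | DE, m=200 | √DE | Actual error |
|---|---|---|---|---|---|---|
| 0.001 | 1.15 | 1.07 | 0.067 | 1.20 | 1.09 | 0.073 |
| 0.005 | 1.75 | 1.32 | 0.138 | 2.00 | 1.41 | 0.165 |
| 0.01 | 2.49 | 1.58 | 0.214 | 2.99 | 1.73 | 0.257 |
| 0.02 | 3.98 | 1.99 | 0.326 | 4.98 | 2.23 | 0.380 |
| 0.05 | 8.45 | 2.91 | 0.500 | 10.95 | 3.31 | 0.554 |

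Example: for m = 150 and ICC 0.01, DE = 1 + 149 × 0.01 = 2.49, √2.49 = 1.58, 1.96/1.58 = 1.24, and the error is 0.214.

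**Step 4: check by simulation.** With 20,000 runs at m = 150, a t-test on change rejected in 0.052 of runs at ICC 0, and in 0.136, 0.219, 0.328 and 0.510 at ICC 0.005, 0.01, 0.02 and 0.05. This agrees with the formula.

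**Step 5: more pupils do not help.** As m grows, the SE of the difference cannot fall below √(2 × ICC): 0.14, 0.20 and 0.32 SD for ICC 0.01, 0.02 and 0.05.

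**The case against.** **The design is openly declared.** The Discussion calls it quasi-experimental with one group of each kind and warns of trouble in interpretation. Sample size gives the same reason for adjusting. This stands as partial disclosure. But the warning concerns differing baselines. Difference-in-differences is offered for those only, and neither clustering nor the identity of school and arm is mentioned.

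**The schools are sampled at random.** This helps to say where they come from. It leaves one school per arm and 0 degrees of freedom, as random allocation of the two schools also would.

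**Not every p value is affected.** A reader might infer that all planned tests are invalid. The article also plans before-after comparisons within each group, and these do not compare schools. The point covers only the between-group tests of the intervention.

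**The inflation rests on an ICC that the article does not give.** This stands. A reader might infer that the p values are certainly too small; that needs an ICC above 0 in the analysed change. At 0.001 the error is only about 7%.

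**One covariate varies over time.** Study variables includes recent exposure to mass-media information, recorded for each evaluation. It partly covers differing outside exposure, but not teaching or events inside a school.

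**A large effect might survive.** If f2 = 0.15 is read as the intervention term alone, d = 2 × √0.15 = 0.77 SD. At ICC 0.05 and m = 150 the inflated SE is √(2 × 8.45/150) = 0.34 SD, so the effect would be 0.77/0.34 = 2.3 SEs. The article more naturally describes a whole-model f2, so this reading is itself an assumption. It does show that a significant result is not automatically uninterpretable as far as random school variation goes. A systematic change in one school remains a bias that no ICC captures.

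**An unseen analysis plan might deal with it.** The level of inference and the number of schools are fixed in this article, and no analysis can recover between-school variance from one school per arm.

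**Conclusion.** The point holds for the between-group intervention contrasts. That school and intervention are fully confounded follows from the design alone. That difference-in-differences does not remove a school-specific change over the four months follows from what the estimator subtracts.

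The size is conditional. It assumes equal school sizes, a normal approximation and an ICC of the analysed change that the article does not state. For ICC 0.001 / 0.005 / 0.01 / 0.02 / 0.05, the nominal 5% becomes about 7 / 14 / 21 / 33 / 50% at 150 per school and 7 / 17 / 26 / 38 / 55% at 200. The second set is closer to the planned intention-to-treat analysis with values carried forward.

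The documents do not support saying that every p value in the study is too small, that the error rate is known to be inflated by a given amount, or that no effect, however large, could be credible.

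**What to change.** 1. **Statistical analysis.** Replace the sentence on the unit with wording such as: *Adolescents are the unit of analysis and schools are the unit of assignment. As each arm has a single school, between-group p values describe only the difference between these two schools.*
2. **Sensitivity table.** Report each between-group contrast also with its SE multiplied by √(1 + (m − 1) × ICC), over a range stated in advance, for example 0.001 to 0.05, with m the number analysed per school. Note beside it that this covers random school variation only. It does not correct systematic school-by-time confounding, and these data cannot check the assumed ICC.
3. **Discussion, limitations.** Add that one school per arm makes school and intervention inseparable, and that difference-in-differences does not remove a change specific to one school.
4. **Conclusion.** Limit it to preliminary evidence from two schools. The closing aim of a large-scale tool goes beyond what this comparison can show.

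The cost is wording and one table. The downside is wider intervals and a more modest claim. Spreading the teens over several schools per arm and analysing with school as the cluster would address the design itself, but it is not cheap. It needs more sites and possibly more authorisations, in a study that already cites financial limits. It is therefore an option, not part of the minimum change.

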3.	It's better to know and care regarding HIV/AIDS and unwanted pregnancy.	1. HIV/AIDS: 1.1 How HIV/AIDS affects health. 1.2 Statistics on the prevalence of HIV/AIDS worldwide and in Mexico. 1.3. Ways of transmission of HIV/AIDS. 1.4 Common symptoms of people with HIV/AIDS: 1.5 Methods of detection and protection. 2. Is there any other risk in addition to STIs? And what if I get pregnant? What if my girlfriend gets pregnant? Teenage pregnancy statistics. Contraceptive methods: pros and cons. 3. Steps to use male and female condoms
4.	Preparing for a pleasant and safe sexual experience. Am I ready?	1. How can I negotiate condom use? Learning strategies for condom use negotiation 2. Tips for condom negotiation: □ at first intercourse □ at intercourse with a stable and casual partner □ when one of the two consumed alcohol □ when both are very excited 3. Make your own comics about how you would negotiate using a condom with your partner 4. E-sites on sexual and reproductive health

Furthermore, during the intervention and follow-up, booster e-mail messages will be sent to the teens of the intervention group. “Booster messages” will emphasize the main points of the educational sections and will be sent two to three times per week from the second week of the intervention.

Information on the study variables will be obtained through the Internet-based self-applied questionnaire and collected on three occasions: 1) when the adolescent enters into the study (baseline), 2) once the intervention is completed (at 1 month) and 3) after 3 months of follow-up (fourth month).

In the control group, teens will continue the usual school-provided sex education and will be invited to answer the Internet-based self-applied questionnaire at the same time as the intervention group. Furthermore, at the conclusion of the study, teens from the control group will also receive access to the educational sessions.

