The proposed intervention has several strengths. (i) Educational materials for this intervention are visually attractive and culturally adopted. (ii) The Internet will be the vehicle to deliver the intervention because it is popular and widely accepted by adolescents and has multiple advantages that we addressed in the Introduction. (iii) The intervention comprises recruitment and retention strategies as previous educational Internet-based interventions have reported rates of participant attrition >25 % [38]. Therefore, use of retention strategies is crucial as the retention of participants is a parameter of the internal validity, feasibility, and acceptability of the study. Furthermore, we anticipated the dropout rate in sample size estimation. (iv) The intervention will also include booster strategies as previous studies found major effects in the intervention groups that incorporated such strategies compared with those that did not [39]. (v) Finally, results of the intervention will be statistically controlled for potential confounding variables including “social desirability”. Previous studies in the field of health-related behaviors have identified the presence of social desirability bias in self-reports of respondents. Social desirability refers to the systematic tendency of individuals to provide a better image of themselves, reporting responses perceived as more socially acceptable [40]. It has been identified that social desirability bias in the participants’ response is similar in the printed paper surveys and anonymous online surveys [41]. Therefore, measurement and control of this bias is recommended [40]. Several scales to assess social desirability exist; however, most were designed and validated for adults. According to our knowledge, only one scale has been designed and validated in English for measuring social desirability in children and adolescents, which is the Children’s Social Desirability Scale [42]. However, this scale is extensive (48 items) and has not been validated in Spanish. At the same time, the “Lie scale” of the “Junior Eysenck Personality Questionnaire” was validated in 25 countries including Mexico. Application of this scale showed that Mexican children and adolescents express greater social desirability compared to U.S. children [31]. Taking into account this background, we decided to measure the desirability bias using the “Lie scale” as well as to control this bias in the statistical analysis.

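### Carrying the last score forward for teens who withdraw, with 25% drop-out planned, can bias the month-1 and month-4 effects in a direction the plan cannot know in advance

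*Protocol article*

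**What the plan says.** Under Statistical analysis, scores missing because of a participant's "withdrawal from the study will be replaced with the most recent observations". This is last observation carried forward (LOCF). It is the only missing-data method in the article, and no sensitivity analysis accompanies it. The same section states: "The analysis will be performed according to the intention-to-treat approach". It also states: "Differences between groups will be compared using the differences-in-differences (D-in-D) estimator". A generalized linear model then adjusts for baseline and covariates and is described as able to handle correlated repeated observations.

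Under Sample size: "The number of teens by group, assuming a drop-out rate of 25 %, will be 200". The 25% is not split by school or by visit. The Discussion, among the strengths, says that "previous educational Internet-based interventions have reported rates of participant attrition >25" per cent.

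After baseline, scores are taken only "once the intervention is completed (at 1 month) and 3) after 3 months of follow-up (fourth month"). A carried-forward value is therefore always either the baseline score or the month-1 score.

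**The concern.** The rule makes a definite assumption about every teen who leaves. One who leaves before month 1 is taken not to have changed at all, at either follow-up. One who leaves after month 1 is taken to hold the end-of-course score for three more months, although that period is where fading or growth of the effect would show. In the control school, teens continue the usual sex education, so zero change is not a safe assumption there either. Filled scores enter the model as though they had been measured.

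What is at stake is the size, and in some circumstances the sign, of the between-school difference on each outcome, judged at p < 0.05. LOCF is sometimes defended as conservative. The working shows that it can shrink an effect, enlarge it, or create one where none exists.

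**Working it through.** **Exposure.** 0.25 × 200 = 50 teens per group with a filled-in final score and 150 with a measured one. The plan gives no figure for the consequence of its rule, so there is none to reproduce. It also gives no SD, expected change, drop-out timing or drop-out by school. All values below are therefore assumptions, in SD units. Drop-out is at random, and leavers follow the same course as stayers unless stated.

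**Formulas.** Let a be the share lost before month 1 and b the share lost between months 1 and 4. D1 and D4 are the mean changes from baseline in the intervention school, c1 and c4 those in the control school, and I and C mark the schools. The expected difference-in-differences under LOCF is:

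- Month 1: E1 = (1 − a_I)·D1 − (1 − a_C)·c1
- Month 4: E4 = [(1 − a_I − b_I)·D4 + b_I·D1] − [(1 − a_C − b_C)·c4 + b_C·c1]

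Month 1 depends only on a, so loss after month 1 cannot affect it.

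**1. Early loss, stable controls.** a = 0.25 in both schools, b = 0, D1 = D4 = 0.40, c1 = c4 = 0. LOCF gives 0.75 × 0.40 = 0.30 at both visits. Observed data give 0.40. The true effect over all enrolled teens depends on what share k of the benefit early leavers would have had: truth = 0.75 × 0.40 + 0.25 × k × 0.40.

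| Share of benefit k | Truth | LOCF bias | Observed-data bias |
|---|---|---|---|
| 1 | 0.40 | −0.10 | 0 |
| 0.5 | 0.35 | −0.05 | +0.05 |
| 0 | 0.30 | 0 | +0.10 |

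**2. Fading effect.** a = 0.05 and b = 0.20 in both schools, D1 = 0.50, D4 = 0.20, controls stable. E4 = 0.75 × 0.20 + 0.20 × 0.50 = 0.15 + 0.10 = 0.25, against a true 0.20 (25% too high).

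**3. Shared gain, no effect.** All changes 0.5, all loss before month 1, 15% in the intervention school and 35% in the control school (average 25%, as planned). LOCF gives 0.85 × 0.5 − 0.65 × 0.5 = 0.425 − 0.325 = +0.10. With the percentages reversed it gives −0.10.

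**4. Growing effect, late loss.** b = 0.25 in both schools, D1 = 0.30, D4 = 0.50, controls stable. E4 = 0.75 × 0.50 + 0.25 × 0.30 = 0.375 + 0.075 = 0.45, against a true 0.50.

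**5. Sustained effect, late loss only.** b = 0.25 in both schools, D1 = D4 = 0.40. E4 = 0.75 × 0.40 + 0.25 × 0.40 = 0.40. There is no mean bias at either visit.

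**Simulation** (200 per group, correlation 0.5 between visits, 4000 runs) agreed with the algebra. In scenario 1 with k = 1, the LOCF 95% confidence interval covered the truth in about 75% to 78% of runs, depending on whether baseline-adjusted or change scores were analysed. With baseline adjustment, the LOCF standard error was 0.079, against 0.100 on observed data. In scenario 2, coverage was still about 92%. In scenario 3, LOCF rejected a true null in about 21% to 23% of runs, against about 5% on observed data.

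**The case against.** The strongest reply is that LOCF is not always the worse choice. Sessions open weekly and in sequence, and month 1 is the end of the course, so teens who leave before then may have had only part of it. Under intention to treat, their lack of benefit belongs in the effect. The k = 0 row of scenario 1 shows this: LOCF is right at 0.30 and the observed-data estimate of 0.40 is too high, with simulated coverage of about 96% against 86%. This stands. It is the reason the fix needs a sensitivity analysis as well as a different main model.

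Second, the article does not say that the effect fades. Booster messages continue through follow-up and are meant to prevent fading, and even the assumed fade costs only 0.05 SD. This also stands as to size.

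Third, a reader might infer more than the documents support:

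- That both follow-up effects are certain to be biased. Month 1 is affected only by loss before month 1. With equal loss and stable controls, that bias is predictably towards the null. Scenario 5 has none.
- That unequal loss favours the intervention. It does so only if both schools improve and the control school loses more teens. The sign reverses otherwise.
- That observed-data analysis is unbiased in general. It was unbiased in the simulations where drop-out was random and leavers would have benefited like stayers. Drop-out linked to disengagement was not among them.
- That a claim of maintained benefit at month 4 would be inflated. The article makes no such claim and names no primary time point.

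None of this rescues the rule. Whether LOCF is harmless depends on timing, fading and imbalance that cannot be known when the plan is fixed.

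**Conclusion.** The point holds as a risk created by a stated rule. It does not rest on a contradiction or a wrong figure. LOCF as the only missing-data method, with a quarter of teens expected to leave, can bias the results. In the scenarios above the bias ranges from −0.10 to +0.10 SD, with the sign set by circumstances the article does not give. The sizes rest wholly on the assumed changes, drop-out splits and random drop-out, so they illustrate the mechanism and do not predict this trial's error. It should be fixed, but it falls short of a defect that must be fixed before the plan can stand.

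**What to change.** Remove carry-forward as the main method. Analyse all observed scores at baseline, month 1 and month 4 in a likelihood-based mixed model with group, time, group-by-time and baseline covariates. Keep every enrolled teen in the group of their school. This model is valid when data are missing at random. The fitting method should be named, because the planned generalized linear model with correlated observations could also be fitted by unweighted generalized estimating equations, which in general need data missing completely at random.

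Add a multiple-imputation sensitivity analysis for data missing not at random. Shift the imputed intervention-school scores downwards over a range stated in advance, and let that range include early leavers having had no benefit. In the units of scenario 1, it would run from no shift to −0.40 for those lost before month 1.

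No new data are needed. The cost is revised analysis wording, a little more analysis work and somewhat wider confidence intervals.

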**Methods:**

A field trial with intervention and comparison group and with ex-ante and ex-post measurements will be conducted in two public secondary schools. Adolescents between 14 and 15 years of age will participate. The intervention will be conducted in one school and the second school will serve as a comparison group where the investigators will observe the usual sex education provided by the school. The intervention will be delivered using an internet web page that includes four educational sessions provided during a 4 week period. Follow-up will last 3 months. Information on the study variables will be obtained through an Internet-based self-applied questionnaire and collected on three occasions: 1) when the adolescents enter the study (baseline), 2) once the intervention is completed (at 1 month) and 3) after 3 months of follow-up (at the fourth month). There will be three outcome variables: 1) knowledge in regard to sexually transmitted infections, 2) attitudes regarding condom use, and 3) self-efficacy toward consistent condom use. The generalized linear model will be used to assess changes in each outcome variable controlling for baseline measures and for study covariates.

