### Study variables

There will be three outcome variables:Knowledge of sexually transmitted infections as measured by the scale validated in Mexican teens by Robles-Montijo and Diaz-Loving [27]. This scale consists of 23 items with a response format “true”, “false” and I don’t know”. The sum of correct answers ranges from 0 (absence of knowledge) to 23 (high knowledge).Attitudes regarding condom use will be measured by the UCLA Multidimensional Condom Attitudes Scale [28]. This scale consists of 25 items and assesses five independent factors: (i) reliability and effectiveness of condoms, (ii) pleasure associated with condom use, (iii) stigma attached to being a condom user, (iv) embarrassment associated with the negotiation and use of a condom, and (v) embarrassment associated with the purchase of a condom. The scale was previously validated in Mexico [29] and has a Likert-type response format with values ranging from 1 (strongly disagree) to 7 (strongly agree) and with an intermediate value of 4 (undecided). Some questions are worded negatively indicating a negative attitude, so the score has to be reversed. Each domain is scored separately producing a score per domain. The domain rating is calculated as the sum of the items in the domain.Self-efficacy toward consistent condom use will be assessed by the seven measures proposed by Fishbein and colleagues [30] and then translated into Mexican Spanish by Robles-Montijo & Diaz-Loving [27]. These include one direct and six indirect measures toward consistent condom use. The direct measure will be obtained by the response to the item ‘Many different things can get in the way of using a condom when people have sex. How sure are you that you can use a condom every time you have vaginal sex with your main partner?’ The response is coded on a 1–7 Likert scale with ‘very sure I cannot’ and ‘very sure I can’ as endpoints. The indirect measure of self-efficacy toward consistent condom use will be obtained using six items. The first five had the commonality of ‘how sure are you that you can (could) always use a condom for vaginal sex?’ The conditions were: (1) when he/she has been drinking or using drugs, (2) when you have been drinking or using drugs, (3) when he/she is very sexually excited, (4) when you are very sexually excited, and (5) when he/she does not feel like using a condom. The final item is focused on an abstinence self-efficacy: ‘what if you and your main partner want to have sex and a condom is not available? How sure are you that you can put off having vaginal sex with your main partner until you or he/she can get one?’ All responses to indirect measures are on a 0─10 scale format where 0 indicated ‘absolutely sure you cannot’ and 10 ‘absolutely sure you can’ [30].

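### Three unranked outcomes, two of them made up of several scores, are measured at two follow-ups and each judged at 0.05, with no primary outcome or time point

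*Protocol article*

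**What the plan says.** The Abstract and the Study variables section both state: "There will be three outcome variables". None is called primary. The article uses that word only for the study objective, at the end of Study variables.

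Study variables then defines the scores:

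- **Knowledge:** one sum score from 0 to 23.
- **Condom attitudes:** "This scale consists of 25 items and assesses five independent factors". On scoring: "Each domain is scored separately producing a score per domain". No total is defined.
- **Self-efficacy:** "These include one direct and six indirect measures toward consistent condom use". The direct item is scored 1–7 and the indirect items 0–10, and no rule for combining them is given.

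After baseline, the section on description and evaluation of the intervention schedules two assessments, at month 1 and at the fourth month. Neither is marked as decisive.

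Statistical analysis compares groups by difference-in-differences and adds: "The generalized linear model (GLM) will be used to assess changes in each outcome variable controlling for baseline measures and study covariates". The threshold is "p value <0.05 will be considered as statistically significant". The Sample size section is not tied to any one outcome, so it does not identify a primary one either.

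**The concern.** Three labelled outcomes look like a small family of tests, but the scoring rules expand them to between 8 and 13 scores, and two follow-ups can double that. A flat 0.05 for each leaves open which result carries the conclusion. A single attitude domain or self-efficacy item, nominally significant at one visit, could then be presented as evidence that the strategy works. The article puts the strategy forward as a large-scale preventive tool, so the error rate of that overall conclusion matters. Leaving the choice of score and time point until the data are in also invites selective emphasis.

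**Working it through.** The plan states no overall error rate, so there is no figure of its own to reproduce on that point.

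**Inputs**
- Per-test threshold 0.05 (Statistical analysis), taken as two-sided because sidedness is not stated.
- Scores (Study variables): 1 + 5 + 7 = 13, or 1 + 5 + 2 = 8 if the six indirect items form one score.
- Two post-baseline time points: 8 × 2 = 16 tests or 13 × 2 = 26 tests, if each time point is tested separately.
- Correlation between test statistics is not given. Independence (0) and a common 0.5 are assumed as the main range, with 0.7 as a stronger case.

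**Formula.** With no true effect on any score and k independent tests, P(at least one p < 0.05) = 1 − 0.95^k. For a common correlation, the same probability comes from equicorrelated normal statistics with cut-off ±1.96.

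| Reading | k | Independent | Corr. 0.5 | Corr. 0.7 |
|---|---|---|---|---|
| Three single outcomes, one time | 3 | 0.143 | 0.125 | 0.109 |
| Three single outcomes, two times | 6 | 0.265 | 0.207 | 0.164 |
| 8 scores, one time | 8 | 0.337 | 0.250 | 0.191 |
| 13 scores, one time | 13 | 0.487 | 0.334 | 0.241 |
| 8 scores, two times | 16 | 0.560 | 0.374 | 0.264 |
| 13 scores, two times | 26 | 0.737 | 0.475 | 0.321 |

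For example, 1 − 0.95^13 = 1 − 0.513 = 0.487.

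A more realistic structure lets correlations differ within a scale, between scales and between visits. For 26 tests, simulation gives 0.67 with assumed values 0.3/0.1/0.5 (within/between/visits), 0.60 with 0.5/0.2/0.5, 0.47 with 0.7/0.3/0.7 and 0.37 with 0.8/0.5/0.8.

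The within-group comparisons and the between-group comparisons of sexual behaviour, which the article also plans, are not counted here and would add tests.

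**Sample size under a stricter threshold.** The Sample size section uses a multiple-regression F test with f² = 0.15 and 15 predictors. Its 0.90, labelled beta, is read here as power. With noncentrality 0.15N and 15 and N − 16 degrees of freedom:

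- alpha 0.05: N = 171 in total, and 171/0.75 = 228 with 25% dropout. This does not reproduce the stated 200 per group, which is a separate matter.
- alpha 0.05/3 = 0.0167: N = 206 in total, and 206/0.75 ≈ 275 with dropout, against 2 × 200 = 400 planned.

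That test concerns all predictors jointly. As a plainer illustration, take an assumed group difference of 0.4 SD with 200 × 0.75 = 150 analysed per group, ignoring covariates and clustering. Power is 0.93 at 0.05 and 0.86 at 0.0167.

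**The case against.** - **The count is an upper bound.** Study variables also speaks of the indirect self-efficacy measure in the singular, obtained from six items, which points towards 8 scores. The repeated-measures model may give one group-by-time test per score, which removes the doubling. Both points stand. The text does not settle either, so the size has to be a range.
- **Independence is the least credible case.** The same adolescents answer every scale at both visits, and five self-efficacy items share one stem. Carrying the last observation forward copies month-1 values to month 4 for those who leave in between. This stands. Calling the domain factors independent describes the scale and does not make the tests independent.
- **No rule says that one significant score proves effectiveness.** Correct: the article defines only what will be called significant. A reader might infer that any one of 16 to 26 tests would establish success, but that is not written. The figures therefore apply on the condition that a single significant score is taken as support.
- **Multiplicity can be left to an analysis plan.** A detailed procedure can. But this text itself lists co-equal outcomes and sets one unadjusted threshold, so the point rests on what is stated.
- **Three co-equal outcomes have a rationale.** The framework covers information, motivation and behavioural skills, to which knowledge, attitudes and self-efficacy plausibly correspond. This is a fair reason not to insist on a single primary outcome.

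**Conclusion.** The point holds. Under every reading of the text the chance of at least one false positive exceeds 0.05. At one time point it is about 13–14% for three tests, 25–34% for 8 scores and 33–49% for 13. With separate tests at both time points it is 37–56% (16 tests) to 48–74% (26 tests). These ranges run from an assumed correlation of 0.5 to independence, and stronger correlation lowers them.

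They assume no true effect on any score and that any significant score would be taken as support. A reader might go further and say that a false positive somewhere is likely. The documents do not support that: it needs most of the 16 to 26 tests to be run separately with weak to moderate correlation. The chance is below one half with one test per score, with three composites, or with strong correlation.

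This is a point the sponsor should correct, with firm confidence in the defect and less in its exact size.

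**What to change.** Before outcome data are analysed, adopt one of two options:

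1. Name one primary outcome score and one time point. The 0–23 knowledge score at month 4 is one possibility, as the only outcome already defined as a single score, but the choice belongs to the sponsor.
2. Keep the three outcomes co-equal at one named time point and apply Holm across them (thresholds 0.0167, 0.025 and 0.05), with one joint test of the five attitude domains and one self-efficacy score defined in advance, including how the 1–7 and 0–10 items are combined or which is used.

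In either case, report the remaining domain, item and other-time-point results as secondary, with confidence intervals and no claims of significance.

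The cost is a change of wording. Option 1 costs no power for the chosen test. Option 2 lowers power per test somewhat, but on the article's own regression basis about 275 enrolled in total would suffice at 0.0167, against 400 planned. Neither option addresses the one-school-per-arm, non-randomised design, so neither by itself brings the error of an overall claim of effectiveness to 5%.
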